	**Detailed Description**
Inclusion criteria	1) Willing and able to participate in this trial, and signed informed consent (sign by the legal representative if patient has no civil capacity)
	2) Aged of 18–60 years old
	3) Weighed of 40–80 kg 4) Respiratory specimen positive for acid-fast bacilli on smear microscopy or positive for *M. tuberculosis* by Xpert® MTB/RIF (Cepheid, Sunnyvale, CA, USA)
	5) Sensitive to rifampicin by molecular or phenotypic susceptibility testing
	6) Has not received any anti-TB treatment in the past 6 months
	7) If female patient not pregnant, willing to apply effective contraception during treatment
Exclusion criteria	1) Combined extrapulmonary tuberculosis
	2) Extensive lesion (extent of disease greater than 50% or the aggregate diameter of all cavities greater than 6 cm) 3) *M. tuberculosis* isolate is already known to be resistant to at least one of the following: isoniazid, pyrazinamide, ethambutol, or fluoroquinolones
	4) Patients with impaired liver function (Alanine aminotransferase or alkaline phosphatase or total bilirubin is higher than 1.5 times the upper limit of normal; hepatic encephalopathy, ascites)
	5) White blood cell is less than normal or hemoglobin is less than 90 g/L or platelet is less than 100*10^9/L
	6) Estimated glomerular filtration rate is less than 90 mL/min/1.73m^2^
	7) HIV antibody positive and AIDS patients
	8) Allergy or intolerance to any study drugs
	9) Unable to take oral medications
	10) If the following drugs are currently or are planned to be used within 6 months of enrollment: quinidine, procaine, amiodarone, sotalol, propylamine, zilasidone or tephenadine
	11) Known history of optic neuritis, alcohol abuse, prolonged QT syndrome or QTcF over 450 ms at baseline, epilepsy, mental illness, diabetes with fundus disease, gout, porphyria, myasthenia gravis
	12) Pregnant or breastfeeding

### Recruitment process

DS-TB patients identified by Xpert® MTB/RIF are being screened to determine whether they meet other eligibility criteria for inclusion. The screening information in this trial includes medical history, signed informed consent, results of physical examination, clinical evaluation, sputum smear, Xpert® MTB/RIF, liver function, renal function, blood routine, blood glucose, blood potassium, hepatitis B and C, HIV testing, pregnancy testing, electrocardiogram, chest radiography, and ophthalmologic examination, including assessment of visual acuity and color vision. After screening procedures, these eligible patients without evidence of resistance to isoniazid, pyrazinamide, ethambutol, and fluoroquinolones will be recruited into this trial.

### Treatment allocation

Online registers will be applied to the patients satisfying the eligibility criteria. To balance the bias of each center from different regions, the randomization is conducted through the online central randomization system stratified by the study sites (sponsored by REDCap) and the presence of lung cavitation. In stage 1, participants will be 1:1:1:1 randomly assigned to the study regimens. In stage 2, if 3 regimens are enrolled, participants will be 1:1:1 randomly assigned into the 3 arms; If 2 arms are enrolled, participants will be assigned with a random ratio of 1:1.

### Duration of follow-up

After screening and baseline assessment, follow-up visits will be conducted every 3 days to 2 weeks in the 8-week intensive phase, every 4 to 5 weeks until the end of treatment, every 12 to 14 weeks at the period of post-treatment until 78 weeks after treatment initiation, and the last follow-up visit is 104 weeks after treatment initiation. All patients undergo intensive monitoring of liver function and blood routine, especially for the first two weeks after the first dose. During the follow-up, physical examination, clinical assessment, weight measurement, sputum smear, sputum culture, blood routine, liver function, renal function, electrocardiogram, ophthalmologic examination, and other adjuvant examinations will be done according to schedule (the Additional file). Study enrollment began in November 2022.

### Sample size assumptions

According to previous studies, the percentage of participants with regimen discontinuation at 8 weeks after the first dose is estimated to be 20%. Using the PASS 15 system (NCSS, Version: 15.0.5), we assumed α = 0.1 and β = 0.2 and calculated that a sample size of 96 cases in each group was required for safety assessment in stage 1. Considering a 4% lost follow-up rate, the number of cases per arm to show safety was calculated as 100 (400 in total).

This sample size of stage 2 was also calculated using the PASS 15 system. Assuming α = 0.05, β = 0.2, according to previous studies, the success rate of the control group was 85.4%, and the success rate of the test group was 84.5%, σ = 6.6%. If stage 2 included three arms for research, according to Bonferroni correction α_1_ = α/2 = 0.025, according to PASS 15 non-inferiority test system, 618 samples were required for each arm. In consideration of 12% of patients not satisfying the criteria for microbiological eligibility and 12% of patients not being assessed, 814 patients were required for each arm, so the total sample size of the two arms was considered to be 2442. If stage 2 was divided into two arms for the study, the significance level was set as α = 0.05 with no correction required. According to the PASS15 non-inferiority test system, 487 samples per arm were required. Considering that 12% of patients did not meet the microbiological eligibility criteria and 12% of patients could not be evaluated, thus the total number was considered to be 1282 with 641 samples needed per group.

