All subjects who have taken at least one dose of the treatment will be included in the safety analysis. The analysis for efficacy in this study will be conducted with modified intention-to-treat (mITT), assessable, and per-protocol populations with primary consideration for mITT results. For the primary outcome measurement in stage 2, the upper bound of the 95% confidence interval for the difference in favorable outcome between the control arm and the rifapentine arms must be less than 6.6% (the margin of non-inferiority) in the mITT populations for the rifapentine regimen to be declared non-inferior to the WHO standardized regimen.

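### If stage 2 runs with three arms, Holm's step-down at the plan's own overall one-sided 0.05 would lift per-dose power from 80.0% to about 85% with no extra patients

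*Protocol article*

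**What the plan says.** The Sample size assumptions section sets the stage 2 error rates ("Assuming α = 0.05, β = 0.2, according to previous studies"). For a stage 2 with two rifapentine doses and control it writes "If stage 2 included three arms for research, according to Bonferroni correction", and sets the level for each dose at half the overall alpha, 0.025. It assumes that "the success rate of the control group was 85.4" per cent and "the success rate of the test group was 84.5" per cent, and concludes that "618 samples were required for each arm". With 12% microbiologically ineligible and 12% not assessed, this becomes 814 per arm and 2442 in total. With a single rifapentine arm, alpha stays at 0.05 and 487 evaluable per arm are needed.

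The Assessment and analysis of outcome section gives one decision rule. The upper 95% bound for control minus rifapentine "must be less than 6.6% (the margin of non-inferiority) in the mITT populations". Meeting this is the only stated condition "for the rifapentine regimen to be declared non-inferior to the WHO standardized regimen". The article does not let the result for one dose change the level at which the other is judged.

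**The concern.** Bonferroni tests each dose at alpha/2 whatever the other dose shows. Once one dose has been shown non-inferior, only one hypothesis remains, and it can be tested at the full alpha without exceeding the overall error rate. Holm's procedure does this. The dose with the smaller non-inferiority p-value is tested at alpha/2. If it succeeds, the other is tested at alpha. The overall error is controlled whatever the dependence between the two comparisons, and every Bonferroni rejection is also a Holm rejection.

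What is at stake is the chance of showing that both advancing doses are non-inferior. That is useful here because the Background section seeks to optimise the rifapentine dose without losing efficacy, given concern about hepatotoxicity. If both doses are shown non-inferior, safety and pharmacokinetic data can inform the choice between them.

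**Working it through.** **Inputs (protocol article).** Control success 0.854, rifapentine success 0.845 for both doses, margin 0.066, power 80%, alpha 0.05 overall and 0.025 per dose, 618 evaluable per arm, 1:1:1 allocation with a shared control (Treatment allocation section).

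**Step 1: reproduce the plan's figures.** n per arm = (z₁₋α + z₀.₈)² × [p_c(1−p_c) + p_t(1−p_t)] / (margin − (p_c − p_t))².

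- Variance term: 0.854 × 0.146 + 0.845 × 0.155 = 0.12468 + 0.13098 = 0.25566.
- Distance to the margin: 0.066 − 0.009 = 0.057; squared, 0.003249.
- One-sided 0.025: (1.960 + 0.842)² × 0.25566 / 0.003249 gives **618**, as stated.
- One-sided 0.05: (1.645 + 0.842)² × 0.25566 / 0.003249 gives **487**, as stated.
- One-sided 0.0125 (0.025 read as two-sided) gives 748, which matches neither.
- Enrolment: 618 / (1 − 0.12 − 0.12) = 813.2, so 814 per arm, and 3 × 814 = 2442.

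The article does not state sidedness, but its sample sizes are reproduced only if the overall alpha is one-sided 0.05.

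**Step 2: joint distribution of the two test statistics.** Each has mean 0.057 / √(0.25566/618) = 2.80. The shared control gives correlation 0.12468 / 0.25566 = 0.488.

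**Step 3: power at 618 per arm** (Z₁ and Z₂ are the statistics for the two doses).

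- Bonferroni, per dose: P(Z₁ > 1.960) = 0.8002.
- Holm, per dose: P(Z₁ > 1.960) + P(1.645 < Z₁ ≤ 1.960 and Z₂ > 1.960) = 0.8002 + 0.0503 = 0.8505.
- Both doses, Bonferroni: P(Z₁ > 1.960 and Z₂ > 1.960) = 0.6861.
- Both doses, Holm: 2 × P(Z₁ > 1.645 and Z₂ > 1.960) − 0.6861 = 0.7866.
- At least one dose, either method: 2 × 0.8002 − 0.6861, or 91.4%.

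| Overall one-sided 0.05, 618 per arm | Bonferroni | Holm |
|---|---|---|
| Per dose | 80.0% | 85.1% |
| Both doses | 68.6% | 78.7% |
| At least one dose | 91.4% | 91.4% |

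A simulation of binomial data (400,000 runs) agrees closely: 79.9% and 85.2% per dose, 67.9% and 78.3% for both.

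**Step 4: error control.** The simulated family-wise error under Holm is 4.7% with both doses at the margin, and 4.9% with one at the margin and the other at 84.5%.

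**Step 5: sensitivity to the other dose.** If the other dose lies at the margin, Holm's power for a dose truly at 84.5% stays at about 80%, a gain of less than 0.1 point. If the other dose equals control (85.4%), it is 86.4%.

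**Step 6: a different overall level.** At overall one-sided 0.025, Holm gives 76.5% per dose and 67.6% for both. The written rule, read as a two-sided 95% interval for each dose, gives 80.0% and 68.6%.

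**The case against.** The strongest reply is that nothing here is wrong. Bonferroni is valid, and a two-sided 95% interval for each dose matches the 0.025 split in the three-arm case. One criterion for both regimens is simple to report, and a sponsor may prefer it. All of this stands: the point is an efficiency gain, and a reader who infers a flaw in error control goes further than the document allows.

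A second reply is that the split appears in a sample size section, so an analysis plan that is not shown could already specify a step-down. That is possible. The published decision rule is nevertheless a single fixed interval, and it would need rewording in either case.

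A third reply is that the whole gain comes from results with 1.645 < Z ≤ 1.960, where the second dose's two-sided 95% interval crosses 6.6%. This is true and is the real cost. The looser level is not foreign to the plan, however, because the single-regimen case is itself sized at one-sided 0.05.

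Three stronger readings are tempting but unsupported:

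- A reader might infer that Holm also gains at an overall one-sided 0.025, where Bonferroni would give 71.3% and Holm 76.5%. The 71.3% belongs to a 97.5% interval rule that the article never states. Against the written rule's 80.0%, 76.5% is a loss.
- A reader might expect Holm to recover what Bonferroni gives up by ignoring the shared control. Holm's first step uses the same alpha/2 and does not.
- A reader might think that two non-inferiority verdicts define the optimal dose. They do not rank the doses. Safety, culture conversion and pharmacokinetics also bear on that aim.

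**Conclusion.** The point holds as an inexpensive, optional improvement, and only if two rifapentine doses advance. At the plan's own overall one-sided 0.05 and 618 evaluable per arm, Holm adds about 5 percentage points to per-dose power and about 10 to the chance that both doses succeed (78.7 − 68.6 = 10.1). It adds nothing to the chance that at least one succeeds.

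The size rests on three assumptions:

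- Both doses truly have about 84.5% success against 85.4%. The gain disappears if the other dose lies at the margin.
- The overall alpha is one-sided 0.05. This is inferred from the reproduced sample sizes, not stated.
- The 95% interval in the decision rule is two-sided, which is the reading that agrees with the 0.025 split.

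**What to change.** Keep 618 evaluable and 814 enrolled per arm. Before any stage 2 outcome data are seen, amend two sections of the protocol.

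- **Sample size assumptions:** state that the overall alpha for stage 2 is one-sided 0.05, and that the three-arm primary analysis uses Holm's procedure at that level.
- **Assessment and analysis of outcome:** state that the dose with the smaller non-inferiority p-value is judged at one-sided 0.025 (two-sided 95% interval against 6.6%). Only if it succeeds is the other dose judged at one-sided 0.05 (two-sided 90% interval against 6.6%). Report the two-sided 95% interval for both doses.

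No patients are added. The cost is a rewritten decision criterion, and a deciding interval for the second dose that differs from its reported 95% interval and has to be explained. If the sponsor does not accept that, or wants an overall one-sided 0.025, Holm should not be adopted for this power gain.

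### One 95% confidence-interval rule for stage 2 cannot match both the two-arm and the three-arm sample sizes, which rest on different one-sided alphas

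*Protocol article*

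**What the plan says.** Under Sample size assumptions, the stage 2 inputs are introduced with "Assuming α = 0.05, β = 0.2, according to previous studies", followed by "the success rate of the control group was 85.4%, and the success rate of the test group was 84.5%, σ = 6.6" (percent). The 6.6% is identified as the non-inferiority margin under Assessment and analysis of outcome. Two designs are then sized:

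- Three arms (two rifapentine arms and control): Bonferroni gives α/2 = 0.025 per comparison, 618 evaluable and 814 enrolled per arm.
- Two arms (one rifapentine arm and control): "the significance level was set as α = 0.05 with no correction required", and "487 samples per arm were required", which becomes 641 enrolled per arm and 1,282 in total.

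The section does not say whether alpha is one-sided or two-sided.

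Under Assessment and analysis of outcome there is one decision rule for stage 2. The quantity judged is "the upper bound of the 95% confidence interval for the difference in favorable outcome between the control arm and the rifapentine arms"; non-inferiority is declared when, in mITT, this lies under the 6.6% margin. The rule draws no distinction between the two designs and does not say whether the interval is one-sided or two-sided.

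**The concern.** The sample size section uses a different alpha for each design, while the decision rule uses one interval level for both. A sample size delivers its stated power only if the final test runs at the alpha used to size it, so at least one design must be out of step with the rule.

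This is the primary confirmatory test. On one reading, a two-arm stage 2 has a noticeably higher chance of missing a regimen that performs as assumed. On the other, a three-arm stage 2 loses the multiplicity control it was sized for. If the interval level is left open until data are in, the choice between 90% and 95% could itself decide whether non-inferiority is declared.

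**Working it through.** **Inputs.** Control 85.4%, test 84.5%, β = 0.2 (Sample size assumptions); margin 6.6 points (Assessment and analysis of outcome); 1:1 allocation in the two-arm case (Treatment allocation); losses of 12% + 12% = 24% (Sample size assumptions).

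**Step 1: reproduce the plan's sample sizes.** Non-inferiority of two proportions, unpooled normal approximation:

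n per arm = (z₁₋α + z₀.₈₀)² × [0.854×0.146 + 0.845×0.155] / (0.066 − 0.009)²

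The variance sum is 0.12468 + 0.13098 = 0.25566, and the denominator is 0.057² = 0.003249.

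| One-sided alpha | (z₁₋α + z₀.₈₀)² | n per arm | In the plan? |
|---|---|---|---|
| 0.05 | (1.645 + 0.842)² | 486.5, so 487 | yes, two arms |
| 0.025 | (1.960 + 0.842)² | 617.6, so 618 | yes, three arms |
| 0.0125 | (2.241 + 0.842)² | 748 | no |

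The inflated figures follow: 487/0.76 = 640.8, so 641; 618/0.76 = 813.2, so 814.

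Had alpha been two-sided, the two-arm design would need 618 and the three-arm design, after Bonferroni, 748. The plan gives 487 and 618. So its alpha is one-sided: 0.05 overall, and 0.025 per comparison with three arms.

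**Step 2: rule read as a two-sided 95% interval.** Its upper bound is a one-sided 0.025 test.

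Power = Φ(0.057 / √(0.25566/n) − 1.960)

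- Three arms, n = 618: 80.0%, as planned.
- Two arms, n = 487: 0.057/0.02291 − 1.960 = 0.53, giving 70.1%. The planned figure is 80%. With the Farrington–Manning variance it is 69.5%.
- To hold 80% with two arms under this rule needs 618 evaluable and 814 enrolled per arm, or 2 × 814 = 1,628 in total, against 1,282.

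**Step 3: rule read as a one-sided 95% bound.** This is a one-sided 0.05 test.

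- Two arms, n = 487: 80.0%, as planned.
- Three arms: each comparison is tested at 0.05 instead of 0.025. The Bonferroni bound on the overall one-sided error becomes 2 × 0.05 = 0.10, not 0.05.

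**Step 4: sensitivity to the analysis set.** The 487 is what remains after both 12% losses. The rule is applied in the mITT population, and the article lists an assessable population separately, so mITT may keep patients who could not be assessed. With only the microbiologically ineligible removed, 641 × 0.88 = 564 per arm. At unchanged success rates, two-arm power under the two-sided 95% interval is then 76.3%. Counting the unassessed as failures would lower both rates and change this figure; the article does not settle which applies.

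**Step 5: if one-sided 0.025 were the overall level in both designs.** Bonferroni would give 0.0125 per three-arm comparison. At n = 618, power is Φ(0.057/0.02034 − 2.241) = 71.3%; 80% would need 748 evaluable per arm.

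**The case against.** The strongest objection is that the rule does not state sidedness, so 70% is the result of one reading only. That stands. A reader might infer that the two-arm trial simply has 70% power; the text does not support that without the condition, because a one-sided 95% bound restores exactly 80%. The two-sided reading is the more natural one, since the stage 1 tolerability rule calls its 90% interval one-sided explicitly and the stage 2 rule does not. It remains an inference, as does the one-sidedness of alpha, which rests on exact reproduction of two separate figures.

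A reader might also suspect an arithmetic error. There is none: 487, 618, 641 and 814 all reproduce. The fault lies between two sections.

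Three further points limit the weight. The two-arm design arises only if a single rifapentine arm meets the stage 1 safety conditions. The Discussion says stage 1 findings will contribute to the stage 2 sample size calculation, so 487 may be revised. And on the two-sided reading the harm is lost power, not more false claims of non-inferiority. All three are fair, but none removes the mismatch. The two-arm case is planned for explicitly, and a recalculated sample size would still need an alpha that agrees with the decision rule. Switching to the one-sided reading only moves the problem to the three-arm design.

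**Conclusion.** The concern holds as an inconsistency between the stage 2 alphas and the stage 2 decision rule. No single 95% interval fits both designs. The size depends on the reading:

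- Two-sided 95%: three arms consistent; two arms at about 70% power with 487 evaluable per arm, or about 76% with 564 in mITT at unchanged rates, against 80% planned. At 487, the chance of missing a regimen as good as assumed rises from 20% to about 30%.
- One-sided 95% bound: two arms consistent at 80%; three-arm comparisons each at 0.05, with no multiplicity correction.

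These figures assume the plan's own success rates and margin and the normal approximation that reproduces its sample sizes. The documents do not support an unconditional statement that power is 70%, or that the false-positive rate is inflated, since each follows from only one of the two readings.

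**What to change.** Under Sample size assumptions, label alpha as one-sided 0.05 overall. Under Assessment and analysis of outcome, state the interval for each design:

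- two arms: upper limit of a two-sided 90% interval (equivalently a one-sided 95% bound) below 6.6%;
- three arms: upper limit of a two-sided 95% interval below 6.6%, for each comparison.

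This follows the levels the plan was sized for, keeps 80% power in both designs and leaves 641 and 814 per arm unchanged. The cost is wording in two paragraphs.

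If the sponsor prefers the two-sided 95% interval for the two-arm design, restate its power at 641 enrolled per arm as about 70% and say that its overall one-sided alpha is 0.025. The overall one-sided error would then be 0.025 with two arms but up to 2 × 0.025 = 0.05 with three, and the article should say so.

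If one-sided 0.025 is meant as the overall level in both designs, each three-arm comparison needs 0.0125 (a two-sided 97.5% interval), and its power at 618 evaluable per arm must be restated as about 71%, alongside about 70% for two arms. Neither alternative needs extra patients if the lower power is accepted.

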### Data collection and quality management

Dedicated websites and data collection forms will be applied by collaborating hospitals or centers for research management to record data. Unique usernames and passwords will control all data access on websites, so staff only have access to the functionality and data that are appropriate for their role in the study restrictedly. The responsibility of the Central Coordinating Office (CCO) staff will be the provision of the relevant website and case report forms. The eligibility of patients and follow-up data completeness will be also checked by CCO regularly. The database will be locked after the completion of the whole follow-up schedule and data review.

### Adverse event management

SRC is established in this trial to review and discuss the existing safety and efficacy data to determine whether the arm is suitable to continue to the next stage and provide professional advice on clinical management strategy. SRC is composed of a powerful clinical team of TB specialists, pulmonologists, infectious disease experts, nephrologists, psychiatrists, cardiologists, hematologists, and rheumatologists. SRC meetings are divided into regular and urgent meetings. Regular SRC meetings will be held for routine safety data review every 2 months. Any SAE must be reported by investigators to the SRC within 24 h, meanwhile, the urgent SRC meeting will be triggered to decide the execution of the related cases and treatment arms, including adjustment of anti-TB regimens, discontinuation of treatment arms, etc. AEs are defined and reported by the site investigator according to the Common Terminology Criteria for Adverse Events 5.0 (CTCAE) [26]. An SAE is classified if it led to death, life threatening, prolonged hospitalization, permanent or serious disability, malformation or congenital defect of the offspring, or required hospital admission for management. All AEs and the adjustment or withdrawal of drugs in this trial will be recorded and checked by CCO.

